## 5.6 Dosages, dosage modifications and method of administration

Salbutamol will be administered intravenously in a single dose injection of 250 µg over the time course of 5 min.

## 5.7 Preparation and labelling of Investigational Medicinal Product

Preparation and labelling of salbutamol will be done by the department Clinical Pharmacy and Toxicology of the LUMC according annex 13 of the guideline Good Manufacturing Practice (2003/94/EG, via [http://ec.europa.eu/health/files/eudralex/vol-4/2009\\_06\\_annex13.pdf](http://ec.europa.eu/health/files/eudralex/vol-4/2009_06_annex13.pdf)) and local law and trial requirements. An example of the label is provided in section D 'Product information'.

## 5.8 Drug accountability

The principal investigator will be responsible for drug accountability and will ensure that the whole research team understands and follows the research protocol. Drug accountability will be cared for by the department Clinical Pharmacy and Toxicology of

the LUMC. The drug accountability record will be filled in during the study days by the sub-investigator and research nurse running the clinical trial. The trial product will only be dispensed to subjects in the trial according to the protocol.

## 6. NON-INVESTIGATIONAL PRODUCT

### 6.1 Name and description of non-investigational product(s)

In this study we use non-investigational products: propranolol, placebo, the radioactive [ $^{18}\text{F}$ ]FDG tracer and several medical devices.

#### *Propranolol and placebo*

During the two study days administration of our investigational product salbutamol will be preceded with either placebo (study day A) or 80 mg propranolol (study day B), given orally divided over two capsules (Figure 3 and 4). Propranolol is a non-selective ADRB1/2 blocker, approved and commonly used in clinical care for the treatment of hypertension, secondary prophylaxis after a myocardial infarction, angina pectoris, hypertrophic obstructive cardiomyopathy, arrhythmias, thyrotoxicosis and as prophylaxis for migraine [36]. In literature the use of propranolol is regarded to be effective to suppress BAT in patients undergoing an [ $^{18}\text{F}$ ]FDG PET/CT for oncology reasons [37-40]. Propranolol administered in a dosage of 80 mg orally two hours before [ $^{18}\text{F}$ ]FDG PET/CT acquisition was shown to almost completely suppress BAT activity [40]. This same method is also mentioned in the guidelines for tumor imaging from the European Association of Nuclear Medicine [41].

In this study, propranolol will be used to reverse activation of BAT after administration of salbutamol by antagonizing its effect on the ADRB1 and B2. The ultimate goal is to show that the effect of salbutamol on BAT is hereupon abolished and thus not mediated via overspill towards the ADRB3.

For a summary of findings from non-clinical and clinical studies regarding pharmacological safety of propranolol we refer to the Summary of Product Characteristics (SPC), which can be found on the website of the 'College ter Beoordeling van Geneesmiddelen' (CBG) (<https://www.geneesmiddeleninformatiebank.nl/nl/>, registration numbers RVG 12638) and to the product specification in appendix D2.

#### *$^{18}\text{F}$ -fluorodeoxyglucose ( $^{18}\text{F}$ -FDG) tracer*

After administration of placebo or propranolol together with salbutamol a dynamic PET/CT scan will be performed with the use of the radioactive tracer [ $^{18}\text{F}$ ]FDG in a dosage of 185 MBq. [ $^{18}\text{F}$ ]FDG is a positron-emitting glucose analogue that is taken up by the sodium-independent glucose transport family (GLUT1, GLUT3 and GLUT4) in the cell membrane of metabolically active tissues. Due to a radioactive label these metabolically active tissues can in turn be visualized using a PET scan. The CT scan in addition provides the anatomical information. The [ $^{18}\text{F}$ ]FDG PET/CT scan is a non-invasive

diagnostic device that is used in clinical care for the quantification of the metabolic activity of tissues. Indications for [ $^{18}\text{F}$ ]FDG PET/CT include, but are not limited to, the detection, differentiation and classification of oncologic malignancies and the detection of inflammatory processes.

The [ $^{18}\text{F}$ ]FDG tracer will be delivered by GE Healthcare B.V. (Steripet®, Eindhoven, the Netherlands). For more information about the [ $^{18}\text{F}$ ]FDG tracer we refer to the summary of product characteristics (SPC), which can be found on the website of the 'College ter Beoordeling van Geneesmiddelen' (CBG)

(<https://www.geneesmiddeleninformatiebank.nl/nl/>, registration numbers RVG 29834) and to the product specification D2.

### *Medical devices*

Table 1 provides an overview of the devices considered as non-investigational medical products (non-IMPs) that are included in this study: PET/CT, the body composition analyzer, the infrared camera and indirect calorimeter. The device, name, manufacturer and LUMC inventory numbers are provided for each non-IMP. All devices are CE marked and will be utilized within their intended use. Further information is provided in the intake forms for clinical research with medical devices.

*Table 1 Overview of non-IMP devices*

| Device                                            | Name                                | Manufacturer                              | LUMC numbers              |
|---------------------------------------------------|-------------------------------------|-------------------------------------------|---------------------------|
| ECG (Screening)                            | ELI™ 280 Resting Electrocardiograph | WelchAllyn, Mortara                       | 16-800-1692               |
| Body composition analyzer                  | InBody720                           | InBody CO., Ltd.                          | 12-091-0149               |
| Bedside monitor including ECG (Study days) | Philips Intellivue MP5              | Philips Healthcare, Best, The Netherlands | 17-800-1688               |
| Indirect calorimeter (2x)                  | Vmax Vyntus CPX                     | CareFusion                                | 17-800-0138 & 17-800-0137 |
| PET/CT scanner                             | Vereos version 2.0.2.26321          | Philips Healthcare, Best, The Netherlands | 17-840-0074               |

## 6.2 Dosages, dosage modifications and method of administration

### *Propranolol and placebo*

Propranolol or placebo will be administered orally 1 hour before the start of the [ $^{18}\text{F}$ ]FDG PET/CT scan. Dosage of propranolol will be 80 mg, divided over two capsules of 40 mg. Placebo will consist of two similar looking capsules as well.

### *[ $^{18}\text{F}$ ]FDG*

A bolus of [ $^{18}\text{F}$ ]FDG tracer will be intravenously injected in a dosage of 185 MBq directly prior to the start of the PET/CT scan.

## 6.3 Preparation and labelling of Non-Investigational Medicinal Product

### *Propranolol and placebo*

Propranolol and placebo will be blindly packed and labelled by the LUMC department Clinical Pharmacy and Toxicology, according annex 13 of the guideline Good Manufacturing Practice (2003/94/EG, via [http://ec.europa.eu/health/files/eudralex/vol-4/2009\\_06\\_annex13.pdf](http://ec.europa.eu/health/files/eudralex/vol-4/2009_06_annex13.pdf)) and local law and trial requirements. An example of the label is provided in section D 'Product information'.

### *[ $^{18}\text{F}$ ]FDG*

[ $^{18}\text{F}$ ]FDG is obtained and delivered by GE Healthcare B.V. (Steripet®, Eindhoven, the Netherlands) at the LUMC. In total, for every subject 185 MBq [ $^{18}\text{F}$ ]FDG is needed. FDG will be ordered by the Nuclear Medicine section of the Radiology department of the LUMC, on request of the research physicians. [ $^{18}\text{F}$ ]FDG will be delivered calibrated at an indicated time point for an indicated subject by GE Healthcare B.V. (Steripet®, Eindhoven, the Netherlands) in standard packaging to the department of Radiology, section of Nuclear Medicine, at LUMC.

## 7. METHODS

### 7.1 Study parameters/endpoints

#### 7.1.1 Main study parameter/endpoint

Glucose uptake by BAT, as measured by dynamic [ $^{18}\text{F}$ ]FDG PET/CT acquisition

#### 7.1.2 Other study parameters

- Resting energy expenditure, as measured by indirect calorimetry
- Serum markers for lipid metabolism (triglycerides (TG), total cholesterol (TC), high density lipoprotein cholesterol (HDL-C), low density lipoprotein cholesterol (LDL-C), free fatty acids)
- Lipid pathway analysis using lipidomic analysis in plasma samples
- Serum markers for glucose metabolism (glucose, insulin)
- Circulating plasma BAT markers (e.g. microRNAs)

### 7.2 Randomization, blinding and treatment allocation

Subjects will be randomized to decide whether they will receive salbutamol in combination with placebo on the first study day (group A), or salbutamol with the addition of propranolol (group B) (see also Figure 3, in chapter 3. 'Study design'). Randomization will be executed by the LUMC department of Clinical Pharmacology and Toxicology. In this study there will be two randomization groups (A and B) with the weight 1:1 divided over two blocks with a size of 5. We will not use stratification. The study will be performed double-blindly.

### 7.3 Study procedures

This study encompasses three visits: one screening visit and two study days.

First subjects will participate in the screening procedure. The screening consists of the informed consent procedure, a medical history questionnaire, anthropometric measurements, a blood draw and an ECG.

#### 7.3.1 Screening

##### *Inclusion and informed consent procedure*

Subjects will be recruited via flyers (see E3), both in the LUMC and in university buildings in Leiden. Hereupon they can approach the researchers via email or telephone. Their eligibility is assessed with a short telephonic interview checking the basic inclusion criteria, after which patient information will be sent by regular mail or email including the informed consent form (see document E1/E2) and flyer

'Medisch-wetenschappelijk onderzoek. Algemene informatie voor de proefpersoon'. After one week of consideration about their decision a screening appointment will be planned. The screening appointment starts with discussing the study information and informed consent form once again in person with the researcher. Thereafter the informed consent form will be signed by the participant and the researcher.

#### *Screening visit*

The rest of the screening visit will include:

- Demographics and medical history
- Anthropometric measurements
- Fasting blood sample
- ECG

An overview of all elements of the screening visit is given in table 2. The subject will be included in the study in case he meets all the inclusion criteria, is willing to participate in the study, and has signed the informed consent.

*Table 2 Overview of the screening visit*

|                                         | Items                                                                                                                                                                                                                                                                                                                                                                                                                                                                   |
|-----------------------------------------|-------------------------------------------------------------------------------------------------------------------------------------------------------------------------------------------------------------------------------------------------------------------------------------------------------------------------------------------------------------------------------------------------------------------------------------------------------------------------|
| Demographics and medical history | Age
Comorbidities
Current and previous used medication
Family history                                                                                                                                                                                                                                                                                                                                                                                          |
| Anthropometric measurements      | Body weight
Body height
Blood pressure, heart rate
Body composition (using the Body composition analyzer InBody720)                                                                                                                                                                                                                                                                                                                                            |
| Fasting blood sample             | Venapuncture for determination of fasting blood glucose, insulin, TC, TG and parameters of liver (ASAT, ALAT, gGT), kidney (creatinine), thyroid function (TSH), electrolytes (including potassium) and a full blood count.

A total of 7.5 mL blood is withdrawn in a SST®II Advance Gel tube of 3.5 mL and an EDTA containing tube of 4 mL, all from Becton and Dickinson®. These samples will be analyzed at the Department of Clinical Chemistry in the LUMC. |
| ECG                              | 12-lead ECG                                                                                                                                                                                                                                                                                                                                                                                                                                                             |

### 7.3.2 Study days

This study encompasses two study days, both will take place in the LUMC. Subjects will be randomized to decide whether they will receive salbutamol in combination with placebo first (study day A) or salbutamol in combination with propranolol (study day B). All measurements during the two study days are identical. Both study days will be performed in the morning after an overnight fast. This means that subjects are not allowed to drink (except water) and eat from 10 PM the evening before, until arrival in the morning. Furthermore, subjects will be asked:

- not to exercise 48 hours in advance;
- not to drink alcohol 24 hours in advance;
- not to drink tea or coffee 24 hours in advance;
- to eat a standardized meal the evening before (options will be given by the researcher).

An overview of the timeline of the two study days and the involved study procedures is given in figure 4.

[figure not shown]

Figure 4 Study procedures.

After arrival anthropometric measurements (including heart rate and blood pressure) will be determined. An intravenous catheter will be placed and a baseline blood sample will be drawn. This will be followed by a resting energy expenditure (REE) measurement for 30 minutes using indirect calorimetry. Directly after the REE measurement subjects will receive either placebo (study day A) or propranolol (study day B). After 60 minutes, heart rate and blood pressure will be measured again (not shown in figure). Then subjects will be placed in the PET/CT scanner and salbutamol will be administered, directly followed by  $[^{18}\text{F}]\text{FDG}$  insertion. First, a low dose CT scan will be performed, followed by dynamic PET acquisition for 60 minutes. While scanning heart rate and rhythm will continuously be monitored. After PET/CT acquisition a blood sample will be drawn, heart rate and blood pressure will be measured and finally REE will be measured for another 30 minutes.

*Anthropometric measurements*

Shortly after arrival (8:00 AM), anthropometric measurements will be performed (weight, height, waist and hip circumference) and heart rate and blood pressure will be measured.

*Blood sampling*

Next, in both arms a catheter will be inserted in an antecubital vein, for venous blood sampling and for administration of salbutamol and [ $^{18}\text{F}$ ]FDG tracer later during the study day. At two timepoints fasted blood samples will be collected: at the start of the study day and after PET/CT acquisition. In these samples we will determine markers for lipid metabolism (TC, FFA, TG, HDL-C, LDL-C, lipidomics) and glucose metabolism (glucose, insulin). Blood for these measurements will be collected in SST®II Advance Gel tubes of 8 mL and blood collection tubes containing ethylenediaminetetraacetic acid (EDTA) of 8 mL. In addition, we will measure electrolytes (sodium, potassium) in a heparin-lithium tube of 4 mL.

The heparin-lithium tube will directly be brought to the Department of Clinical Chemistry in the LUMC to quickly obtain information about electrolyte levels. The EDTA tube will after blood collection immediately be put on ice and centrifuged promptly (2,000 g at 4°C, for 10 minutes). The SST®II Advance Gel tubes must coagulate for 30-45 minutes before centrifugation. After centrifugation plasma and serum from both tubes will be divided in separate plastic tubes and frozen (-80°C) until assay. Material of all included patients from the SST®II Advance Gel tubes and EDTA tubes will be collected first and then above research markers will be determined all at once at the Department of Endocrinology of the LUMC. The 'rest material' will be stored in the LUMC Biobank Endocriene Ziekten for later additional analysis. For this material the rules and regulations of the LUMC Biobank Endocriene Ziekten are applicable.

An overview of the blood collection during the screening and the study days is provided in table 3.

Table 3 Blood collection during screening visit and study days

| Timepoint         | Measurement                                                                                                                      | Tubes                                                                                   | Amount                                           |
|-------------------|----------------------------------------------------------------------------------------------------------------------------------|-----------------------------------------------------------------------------------------|--------------------------------------------------|
| Screening  | TC, TG, FFA,
Lipoproteins,
Glucose, Insulin,
Liver-, kidney-,
Thyroid function,
Electrolytes, Full
blood count | SST®II Advance
Gel tube (3.5 mL)
EDTA tube (4 mL)                                 | 7.5 mL                                           |
| Study days | TC, TG, FFA,
Lipoproteins,
Glucose, Insulin,
Sodium, Potassium,
Lipidomics,
BAT markers
(miRNAs)               | SST®II Advance
Gel tube (8 mL)
EDTA tube (8 mL)
Heparin-lithium
tube (4 mL) | 20 mL per
timepoint

4x20 mL = 80
mL |
|                   |                                                                                                                                  |                                                                                         | 87.5 mL                                   |

*Energy expenditure measurement*

At two time points (after the first blood sample and after [ $^{18}\text{F}$ ]FDG PET/CT scan) resting energy expenditure will be measured for 30 minutes with a respiratory gas analyzer using a ventilated hood system (Vyntus Canopy). The volume of inspired oxygen and exhaled carbon dioxide will be measured every minute. Using previously described formulas resting energy expenditure will be calculated [42].

*Administration of medication*

When the first resting energy expenditure measurement has finished, subjects will receive either placebo or 80 mg propranolol per oral. Propranolol will be completely absorbed after oral administration and reaches peak plasma concentrations after 1-2 hours. Therefore, administration of placebo or propranolol will be followed by an hour of rest. Subjects can bring something for entertainment (i.e. a book, magazine, music, etc.), but will not be left alone without supervision of a sub-investigator or research nurse.

After an hour of rest, the study day will continue. Vital signs will be measured again to check whether heartrate and systolic blood pressure meet the accepted values of <100 beats per minute and <140 mmHg, respectively. Then subjects are placed in supine position within the PET/CT scanner and salbutamol will be administered via an

IV injection over a time course of 5 minutes. Administration of salbutamol is directly followed by the administration of a bolus of [ $^{18}\text{F}$ ]FDG tracer in a dosage of 185 MBq using an injection pump.

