### 3.4 Sample size calculation

For this study the main outcome parameter is net glucose uptake by BAT after administration of salbutamol, as measured by dynamic  $^{18}\text{F}$ -FDG PET-CT scan.

Our sample size calculation is based on the results recently published by Blondin et al.[1] and Orava et al. [25]. Blondin et al. showed net glucose uptake by BAT as measured by dynamic  $^{18}\text{F}$ -FDG PET/CT after administration of the maximal allowable dose mirabegron (200 mg) of  $22 \pm 14$  nmol/g/min. We expect the effect of salbutamol on glucose uptake by BAT to be at least as big as the effect of the maximal allowable dose mirabegron. Orava et al. [25] showed net glucose uptake by BAT in thermoneutral condition of  $9 \pm 4$  nmol/g/min. Therefore, we predict the net glucose uptake of salbutamol in combination with propranolol to be comparable to the net glucose uptake by BAT in thermoneutral condition. Thus, we consider a difference in net glucose uptake by BAT of  $+13$  nmol/g/min after salbutamol administration as clinically relevant, with a SD of 10,  $\alpha = 0.01$ ,  $\beta = 80\%$ . Based on these parameters we need 10 subjects (<http://biomath.info/power/prt.htm>; based on Snedecor & Cochran, Statistical methods 7th edition).

In case a subject is withdrawn from the study before finishing all measurements, the investigator will try finding a replacement to maintain the initial population size.

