#### *Hypokalemia*

Hypokalemia may occur after IV administration of salbutamol, an effect that is potentiated by hypoxia and concomitant treatment with xanthine derivatives, steroids and diuretics [26]. In this study we will only include healthy subjects that are not suffering from bronchospasms and are thus not hypoxic. In addition, we will exclude subjects that use one of the aforementioned drugs. During the screening visit, at the start of the study day and at the end of the study day we will monitor serum potassium levels.

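### Section 7.3.2 does not hold a man's evening meal option or his caffeine intake constant across his two study days, which adds avoidable noise to comparisons based on 10 pairs

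*Protocol*

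**What the plan says.** Section 9 of the protocol compares salbutamol plus placebo with salbutamol plus propranolol by within-subject tests. Section 3.4 sets the size: "Based on these parameters we need 10 subjects".

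Section 7.3.2 fixes how subjects prepare for each study day. They take nothing but water from 10 PM, do no exercise for 48 hours and drink no alcohol for 24 hours. Two further instructions matter here:

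- Meal: "to eat a standardized meal the evening before (options will be given by the researcher").
- Stimulants: "not to drink tea or coffee 24 hours in advance".

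The section does not say that the meal option taken before the first study day must be repeated before the second. It names no caffeine source other than tea and coffee.

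**The concern.** In a two-day crossover, differences between men drop out of the contrast, but differences between one man's two days do not. Preparation therefore has to match within a man; whether it matches between men matters much less. Both bullets are evidently meant to secure this, and both stop short.

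A choice of standardized meals standardizes the menu. It does not make one man's two evenings alike. A restriction on tea and coffee leaves cola, energy drinks and similar products open on one day, when the man may not use them on the other.

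Energy expenditure, free fatty acids, triglycerides, glucose and insulin are the outcomes most plausibly sensitive to the previous evening's meal and to stimulants. An effect on glucose uptake by brown fat is possible but less direct. With 10 pairs there is little averaging to absorb such variation, and it cannot be removed afterwards.

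**Working it through.** **What the two rules leave open.** Arrival is at about 8:00 AM. Counting 24 hours back from arrival, the tea and coffee restriction starts at 8:00 AM the day before. The water-only rule starts at 10 PM. Between those times, 14 of the 24 hours, caffeine in any form other than tea or coffee is not excluded by the preparation rules. For the meal, any pair of options across the two evenings complies with the text.

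**The plan's own sample size.** Inputs from section 3.4: difference 13 nmol/g/min, alpha 0.01 (sidedness not stated, taken as two-sided), power 80%, and the SD given as "as clinically relevant, with a SD of 10".

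- Normal approximation: n = ((2.576 + 0.842) × 10/13)² = 6.91.
- Adding 3 pairs as a small-sample allowance at the 1% level: 9.91, so 10. The stated figure reproduces.
- Exact paired t: noncentrality 13/10 × √10 = 4.11 on 9 degrees of freedom. Power at n = 10 is 77.7%, and 80% needs 11.

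The plan therefore has no reserve by the exact calculation.

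**What extra day-to-day noise would do.** The documents give no SD for meal or caffeine variation, so the values below are assumptions. If such noise adds an independent SD of e to the within-man difference, on top of 10, the SD becomes √(100 + e²):

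| Assumed extra SD of the difference (nmol/g/min) | SD of the difference | Power, n = 10 | n for 80% |
|---|---|---|---|
| 0 | 10.00 | 77.7% | 11 |
| 1 | 10.05 | 77.2% | 11 |
| 2 | 10.20 | 75.8% | 11 |
| 3 | 10.44 | 73.4% | 11 |
| 5 | 11.18 | 66.3% | 13 |

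Noise with SD s on each day adds s√2 to the SD of the difference, so the row for 3 corresponds to about 3/√2 = 2.1 per day.

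**If the SD of 10 already contains this noise.** Removing a component of SD 1, 2 or 3 from the difference then raises power to 78.2%, 79.6% or 82.1%. Which case applies cannot be told. Section 3.4 does not describe the 10 as an SD of within-man differences. It lies close to the pooled SD of the two cited results, √((14² + 4²)/2) = 10.3.

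**Energy expenditure and blood markers.** No comparable figure can be given, because the protocol states no expected difference or SD for them.

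**The case against.** The strongest reply is that this is operational detail with no demonstrable effect. Preparation is already well controlled by the overnight fast, the standardized meal and the limits on exercise, alcohol, tea and coffee. The subject information is not among the documents and may add instructions. The options may also be close in composition. Energy expenditure and blood are measured before the capsules as well as after the scan, so an analysis of change could remove part of any day effect. Plasma glucose enters the primary endpoint as a value measured on the study day, so a glucose difference between days is not simply unmeasured noise.

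Much of this stands. It is why no size can be claimed and why the effect on the PET endpoint is only possible. It does not answer the wording: the protocol chose to fix these two conditions and did so in terms that a subject can meet without being alike on both days. Instructions written from this text would tend to carry the same gap. The PET scan is done once per study day, so it has no same-day baseline to subtract.

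A reader might infer more, in four ways that the documents do not support:

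- **A contradiction within section 7.3.2.** The sentence "All measurements during the two study days are identical" is about the measurements. Meals and caffeine are preparation, so nothing is contradicted.
- **A false propranolol effect.** Section 7.2 randomises the order and blinds it. Meal option and caffeine use are then unrelated to treatment in expectation, and chance imbalance is sampling error that the test allows for.
- **A hypokalaemia risk from caffeine.** Section 5.4 speaks of "concomitant treatment with xanthine derivatives, steroids and diuretics", and section 3.3 likewise of medication. Extending that to drinks would need outside sources.
- **A calorimeter problem.** Table 1 in section 6.1 lists "Indirect calorimeter (2x"), but it is a device inventory. No rule has a man change units, ordinary conduct would settle the matter, and the calorimeter has no bearing on the PET endpoint.

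**Conclusion.** The point holds as a cheap improvement. Section 7.3.2 allows a man's meal option and his caffeine intake from sources other than tea and coffee to differ between his two study days, and every comparison rests on the difference between those days. The expected cost is lost precision, mainly for energy expenditure and the blood markers and possibly for the PET endpoint.

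The size is unknown. Under an assumed extra SD of 1 to 3 nmol/g/min in the within-man difference, power for the primary endpoint falls by about 0.5 to 4 percentage points from 77.7%; at 5 it falls by about 11 points. These figures assume independent noise added to an SD of 10, a two-sided alpha of 0.01 and a paired t-test. They show sensitivity and are not estimates. The stated sample size of 10 is not shown to be wrong by this point.

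**What to change.** Change two bullets in section 7.3.2 and carry the same wording into the subject instructions:

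- **Meal:** the subject eats the same standardized meal option on the evening before both study days. The option eaten is recorded at the first study day and repeated before the second.
- **Caffeine:** the subject takes no caffeine-containing drinks or products, including tea, coffee, cola and energy drinks, during the same 24 hours.

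This needs no extra visit, sample, staff or equipment. The downside is slightly less free choice for the subject. The change can only help precision, whichever size the variation has.
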